### Protocol

The TIVA group will receive propofol for both induction and maintenance of general anesthesia. The GAS group will receive one or more volatile anesthetics (sevoflurane, desflurane, or isoflurane) for induction and maintenance of anesthesia during the surgery. For the GAS group, propofol, midazolam, remimazolam, etomidate, or ketamine can be used with inhalation agents as co-induction agents at the discretion of the attending anesthesiologist. There are no protocol-specific restrictions for concurrent medication in this pragmatic study. In both groups, adjuvant drugs, such as opioids, ketamine, lidocaine, dexmedetomidine, and neuromuscular blocking agents will be administered according to standard institutional procedures at each site, as is postoperative analgesia including neuraxial or regional blocks.

All participating patients, regardless of the study arm into which they are randomized, will be monitored and managed following general standard-of-care practices aimed at maintaining optimal conditions. Both intraoperative and postoperative management (unrelated to anesthetic management) will be decided by the attending physicians, following the established protocols at each center. However, in order to ensure a high standard of anesthetic management, several common strategies have been established: before surgery, the surgical procedure (video- or robot-assisted thoracic surgery or thoracotomy) will be chosen by the attending thoracic surgeon at each center based on clinical features including patient age, comorbid disease, pulmonary function, and tumor characteristics. Appropriate antibiotic prophylaxis will be administered, and standard pharmacological prevention of postoperative nausea and vomiting will be utilized per institutional practice.

During surgery, intraoperative monitoring will include an electrocardiogram, pulse oximetry, capnography, temperature monitoring, anesthetic depth analysis (bispectral index or patient state index), neuromuscular blockade (with a train of four), and blood pressure measurements. Airway management will follow the administration of a neuromuscular blocking agent. The choice of lung isolation device will be at the discretion of the attending anesthesiologist; it is anticipated that most cases will be performed using either a double-lumen endotracheal tube or a bronchial blocker. The device position will be confirmed by fiberoptic bronchoscopy. Anesthesia will be maintained with either propofol or volatile anesthetics based on randomization; opioids, neuromuscular blocking agents, and other adjuncts will be used at the discretion of the anesthesiologist. Propofol and inhalational anesthetics will be titrated to maintain a bispectral index of 40–60 or a patient state index of 30–50 during surgery. Protective ventilation is conducted after the alveolar recruitment maneuver. Mechanical ventilation is maintained with tidal volume (TV) 6–8 mL per kg of predicted body weight (PBW) and positive end-expiratory pressure (PEEP) 5–15 cm H_2_O during two-lung ventilation and TV 4–6 mL per kg of PBW and PEEP 5–15 cm H_2_O during one-lung ventilation, with I:E ratio of 1:1.5–1:2.5 and the ventilation rate is adjusted in the range of 10 to 20 beats per minute to maintain end-tidal carbon dioxide between 35 and 45 mm Hg. The maintenance fluid is the crystalloid solution, infused at a rate of 2 to 5 mL per kg per hour (Lohser 2008). Leukocyte-depleted allogeneic blood will be administered only as necessary to maintain the prospectively determined target hemoglobin. Because hypothermia impairs immune function (Kurz et al. 1996), we will keep patients normothermic—a distal esophageal temperature ≥ 36 °C—with forced-air warming. Tracheal extubation will be at the completion of surgery if postoperative ventilator support is not required. If the patient is returned to the operating room for reasons such as bleeding control, the same anesthetic should be used.

Postoperative analgesia will be achieved based on institutional practice, patient-specific contraindications, and anesthesiologist and surgeon preference. It is anticipated that analgesia will be accomplished based on combinations of neuraxial techniques, regional blocks, and/or intravenous analgesic medications. After approximately 24 h, it is anticipated that patients will be transitioned to primarily non-opioid-regimens (e.g., acetaminophen, tramadol, non-steroidal anti-inflammatory analgesics); however, oral opioids will also be permitted as needed. Maintenance fluid will be administered to maintain a net fluid balance of 0 postoperatively. Ambulation will be encouraged postoperatively as will physiotherapies based on institutional practice (e.g., deep-breathing exercises, incentive spirometry, and chest physiotherapy by physiotherapists and assigned nurses during the intensive care unit and ward stay). Oxygen will be supplied via face mask, nasal prong, continuous positive airway pressure, non-invasive positive pressure breathing, or high flow nasal oxygen supply in patients with SpO_2_ < 90% postoperatively.

### Measurements

Demographic characteristics, details of general anesthesia, drug use including opioid consumption, surgical procedure, and postoperative pain management protocol will be recorded in the eCRF (Bilfinger et al. 1998; Cronin-Fenton et al. 2015; Flores et al. 1996; Freier and Fuchs 1994; Jaeger et al. 1998; Wigmore and Farquhar-Smith 2016; Yeager et al. 2002).

We will also record prognostic factors related to the risk of NSCLC recurrence, including cancer stage, cell type, tumor size, invasion of blood vessels/lymphatics/perineural/visceral pleura, tumor necrosis, and genetic mutation status, based on pathology reports. We will also record whether resection margins are clear of tumor and whether preoperative or postoperative adjuvant therapy was used. For staging, we will use the 8th edition of TNM definitions in lung cancer (2017) which is issued by the International Association for the Study of Lung Cancer. Follow-up of patient records (tumor-specific variables, such as pathologic cancer stage, any metastasis, and different prognostic markers (gene expression) will be extracted by record-linkage, combining the unique individual number with each hospital or national registry at follow-up. If this is not available, patients and their healthcare providers will be contacted for the information.

Cancer recurrence and all-cause mortality will be evaluated by tracking patients at 3 years after surgery. The patient’s medical chart will be reviewed to confirm recurrence status and to obtain details of recurrence if there is one. We will also obtain the results of the chest computed tomography that is performed routinely in these patients. Biopsy results will be obtained whenever possible. The site of initial recurrence will be determined. If patients are lost and their cancer prognostic or survival data are unavailable from the hospital system in participating sites, the investigators will contact the patients or their guardians directly by phone. Cases of apparent recurrence are adjudicated at the trial coordinating site (SMC: Adjudication Committee), using all available laboratory and clinical evidence, provided by the investigators who will still be blinded.

OS after surgery can be ascertained reliably through various sources including querying the National Death Registry, which is the gold standard for vital status in Korea. Other participating centers will use each country’s corresponding data source. The social security number will also be used to determine mortality for patients who are otherwise completely lost to follow-up if allowed by the IRB in each country. Patients who die without local recurrence or metastatic disease will also be censored at the time of death. All measurement variables are listed in Table 1.

**Table 1 Tab1:** Perioperative data to be collected

Period	Data
Preoperative data	Surgery date Study center Age Sex Weight Height Body mass index Race ASA Physical Status Smoking status Functional status (The Eastern Cooperative Oncology Group [ECOG] performance status) Unrestricted clear fluid ingestion until 2 h before anesthesia Unrestricted CHO-contained fluid ingestion until 2 h before anesthesia Charlson Comorbidity Index Neoadjuvant therapy Clinical stage (The American Joint Committee on Cancer [AJCC] 8th
Operative data	Operative approach Operation name Duration of surgery Duration of anesthesia Intraoperative fluid volume Intraoperative transfusion Intraoperative use of steroids Intraoperative use of opioid Intraoperative adjuvants (ketamine, dexmedetomidine, lidocaine, Steroids, NSAIDs) Use and type of analgesia
Postoperative data	Pathological stage (AJCC 8th) Cell type Tumor size Resection margin Vascular invasion Lymphatic invasion Perineural invasion Visceral pleural involvement Tumor necrosis Mutation Postoperative adjuvant treatment Date of hospital discharge Date of local recurrence Date of metastasis Date of death Cause of death Postoperative complications (Clavien-Dindo classification, STS general thoracic surgery databases) Additional surgeries during the follow-up period and their reason Date of last follow-up

Follow-up chart review, and contact with patients, families, and caregivers will be conducted by outcome assessors who are strictly blinded to group assignment and intraoperative management; questions that might unblind the outcome assessor will be specifically avoided.

Predefined complications are monitored by medical chart review at 7 days or hospital discharge date whichever comes first and recorded in the eCRF.

In accordance with the principles of Good Clinical Practice (GCP), monitoring of the study is arranged by the Sponsor (SMC, Seoul, Korea). SMC is appointed to monitor this study for the Korean sites and for the central monitoring of the database. For the other international sites, the sponsor appoints a local monitoring organization to perform on-site monitoring activities and regular contacts.

The independent data management of the clinical database is managed by the SMC, based on a specific Data Management Plan (DMP). The eCRF serves as the clinical database for the study. In addition, the SMC is responsible for set-up, support, and management of the eCRF. Data management also includes handling queries to resolve any inconsistencies detected by the quality control procedures. eCRF data are subject to both logical computerized checks and manual validation checks against listings in accordance with the study-specific DMP. All inconsistencies detected during these procedures are resolved through queries, being issued to the investigational site personnel.

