### Outcomes

#### Primary and secondary outcomes

The primary outcome of this study is recurrence-free survival (RFS) after curative resection of NSCLC. The observed time-to-recurrence is defined as the duration from the date of surgery to the earliest date between the recurrence/metastasis date and the last follow-up date due to death from any cause, any uncontrollable factor during the study, or the end of the study.

Secondary survival outcomes are locoregional RFS (LRFS), metastasis-free survival (MFS), overall survival (OS), and cancer-specific survival (CSS). The observed time-to-events for LRFS and MFS are defined similarly to that of RFS. The observed time-to-event for OS is defined as the duration from the date of surgery to the earliest date among the date of all-cause death and the last follow-up date due to any uncontrollable factor during the study, or the end of the study. The observed time-to-event for CSS is defined as the duration from the date of surgery to the earliest date among the date of cancer-specific death, and the last follow-up date due to death from any cause other than cancer-specific death, any uncontrollable factor during the study, or the end of the study. Other secondary outcomes are postoperative complications. The postoperative complication is a composite outcome defined as any complication occurring within 7 days post-surgery or at discharge if earlier. The applicable complications are defined by the Society of Thoracic Surgeons (STS) general thoracic surgery databases (Crabtree et al. 2018), and the Clavien-Dindo classification (Wong, Oliver, and Moonesinghe 2017). The postoperative complication is a reasonable surrogate for an immediate postoperative outcome, which we believe will be similar between study groups based on Pasin et al.’s meta-analysis of short-term mortality after propofol vs. volatile anesthesia (95 studies, *n* = 9806 total patients) (Pasin et al. 2015).

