##### Analyses of primary outcome

The rates of RFS will be estimated using the Kaplan–Meier method and will be compared between two intervention groups using two-sample log-rank tests. A univariable Cox proportional hazards regression will be conducted to estimate the hazard ratio for recurrence in TIVA versus GAS groups. As this is a large, randomized trial, we expect that enough number of subjects can be accrued without severe unbalance in each level of major confounding factors such as cancer stage. Multivariable analyses will be further performed to account for possible confounding because they usually can increase the precision of the estimated treatment effect and thus add power to the trial (Canner 1991). In the multivariable Cox proportional hazards regression model, the treatment effect will be estimated after adjusting these confounding factors: center, age, sex, ethnic origin, type of surgery, cancer stage, cell type, tumor size, resection margin, invasion of vascular/lymphatic/perineural/visceral pleura, tumor necrosis, pre-and postoperative adjuvant treatment, major gene mutation status, amount of intraoperative opioids, use of regional analgesia and some covariates with *p* value less than 0.1 in the univariable model (Maher et al. 2014; Sessler et al. 2019). Adjusted survival curves will be drawn to present survival probabilities estimated by univariable or multivariable Cox regression models.

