Anticipating a potential difference in postoperative care between centers, we expect that there would be a difference in treatment effect (i.e., the hazard ratio for recurrence in the TIVA group versus the GAS group) between centers. Therefore, a stratified analysis or a clustered analysis will be performed to account for the between-center difference. The violation of the proportional hazards assumption will be visually inspected by Schoenfeld residual plots. If there is a severe violation of the proportional hazards assumption, various advanced methods such as accounting for time-varying confounder or time-dependent effects will be adopted. If a sample size allows, we will conduct subgroup analyses, in which subgroups are constructed according to each cancer type, cancer stage, age group, and sex. These analyses may help identify specific subgroups of patients for whom the intervention appears especially helpful or not helpful. For sensitivity analysis, Fine and Gray’s test will be used to compare cumulative incidence curves for RFS if competing risks due to non-cancer deaths exist.

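### The primary endpoint is named recurrence-free survival but censors deaths without recurrence, so the planned RFS rates are not RFS and the test is of recurrence only

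*Protocol article*

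**What the plan says.** Under Primary and secondary outcomes the article states: "The primary outcome of this study is recurrence-free survival (RFS) after curative resection of NSCLC". The same paragraph ends observation at the earlier of recurrence or metastasis and "the last follow-up date due to death from any cause, any uncontrollable factor during the study, or the end of the study". Death thus closes follow-up without being an event. Measurements makes this explicit: "Patients who die without local recurrence or metastatic disease will also be censored at the time of death". Locoregional RFS and metastasis-free survival are defined by analogy.

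Under Analyses of primary outcome, "The rates of RFS will be estimated using the Kaplan–Meier method", the arms are compared by log-rank test, and a univariable Cox model is to "estimate the hazard ratio for recurrence in TIVA versus GAS groups". As a sensitivity analysis, Fine and Gray's method "will be used to compare cumulative incidence curves for RFS if competing risks due to non-cancer deaths exist".

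The hypothesis appears in two forms: higher RFS in the Abstract, lower local or metastatic recurrence in the Background. Sample-size calculations says the trial is sized on RFS but enters a 3-year recurrence rate of 20% in the GAS arm. The title of Table 2 speaks of RFS rates, while its footnote defines risk reduction by recurrence rates.

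**The concern.** RFS, by its name, is the probability of being alive and free of recurrence, so death is a failure. Here death without recurrence is censored. The label, the definition and the curve then describe different quantities:

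- A Kaplan-Meier curve that censors these deaths is not RFS, because it leaves out a way of failing.
- Its complement is not the actual probability of recurrence either, because it treats patients who have died as if they could still relapse.
- The sensitivity analysis treats death as a competing risk for RFS. If the endpoint were RFS, death would be part of the event and could not compete with it.

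At stake is the headline result. A significant test would support a lower hazard of recurrence. The Abstract's wording would lead to a report of higher RFS, with 3-year percentages that a reader would take as the chance of being alive without recurrence.

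**Working it through.** **1. The plan's own figure.** With the Schoenfeld formula for a Cox model, 1:1 allocation, two-sided alpha 0.05 and 80% power:

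D = (1.960 + 0.842)² / (0.25 × B²), N = D / P.

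With B = ln(1.2) rounded to 0.18 and P = 0.20, D = 7.849 / 0.0081 = 969 and N = 969 / 0.20 = 4845. Then 4845 / 0.9 gives 5384 enrolled. Both match the article. P is the recurrence rate, so the trial is sized on recurrences alone, which agrees with the definition and not with the label.

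**2. Assumptions for the size of the mismatch.** The article gives no rate of death without recurrence. Let q be the 3-year risk of such death in the absence of recurrence, assumed to be 2%, 5% or 8%. Hazards are constant: recurrence in GAS −ln(0.80)/3 per year, multiplied by 0.83 in TIVA; death −ln(1−q)/3, equal in both arms.

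**3. What the planned curve shows.** It ignores q: GAS 80.0%, TIVA 0.80^0.83 = 83.1%, difference 3.1 points.

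**4. What true RFS would be.** RFS = (recurrence-free probability in step 3) × (1−q). The actual risk of recurrence is [recurrence hazard / total hazard] × (1 − RFS).

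| q (assumed) | True RFS, GAS | True RFS, TIVA | Difference (points) | Actual recurrence risk, GAS |
|---|---|---|---|---|
| 2% | 78.4% | 81.4% | 3.0 | 19.8% |
| 5% | 76.0% | 78.9% | 2.9 | 19.5% |
| 8% | 73.6% | 76.4% | 2.8 | 19.2% |

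The reported level would be 1.6, 4.0 or 6.4 points above true RFS in GAS. With equal death hazards the between-arm difference hardly moves (about 0.1 to 0.25 points).

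**5. If death hazards differ.** As an illustration only, take q = 5% in GAS and double the death hazard in TIVA, with the recurrence hazard ratio still 0.83. The planned analysis shows 80.0% against 83.1%, a hazard ratio of 0.83 and about 78% power. True RFS is 76.0% against 75.0%, with a hazard ratio of 1.05. The cumulative incidence of recurrence is 19.5% against 16.1%, so the competing-risk sensitivity analysis would also favour TIVA.

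**6. If death were made an event.** At q = 5% and N = 4845:

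- Anaesthesia does not affect these deaths: with cumulative hazards of 0.223 (recurrence) and 0.051 (death), the combined hazard ratio is (0.223 × 0.83 + 0.051) / (0.223 + 0.051) = 0.862. There are about 1092 events, power is 69%, and about 6300 evaluable patients are needed for 80%.
- The hazard ratio of 0.83 applies to them too: TIVA RFS is 0.76^0.83 = 79.6%, so events are 2422.5 × (0.240 + 0.204), about 1075, and power is 86%.

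**The case against.** Apart from its name, the endpoint is largely coherent. The Background hypothesis, the definition, the Cox hazard ratio and the sample size all concern recurrence. Log-rank and Cox analyses that censor deaths compare cause-specific hazards of recurrence. They do not need the assumption that those who died would have relapsed like the survivors; that matters only when the Kaplan-Meier curve is read as a probability. This stands, so a reader who infers that the primary test is invalid goes too far.

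A reader might also infer that the trial would overlook a treatment that causes deaths before relapse. The documents do not support that. All-cause overall survival and cancer-specific survival are named secondary outcomes, deaths are sought through registries, and cause of death is collected. The article also expects similar short-term outcomes, citing a meta-analysis. The reversal in step 5 needs an assumed doubling of the death hazard. What remains is narrower: neither the primary endpoint nor its sensitivity analysis would register such an excess.

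Nor should the 1.6 to 6.4 points be set against the 3-point target effect. The first is a shift in level within an arm, the second a contrast between arms.

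The condition "if competing risks due to non-cancer deaths exist" will almost certainly be met in some 4845 surgical patients followed for 3 years, so its conditional form matters little in practice. But the analysis remains secondary, names only non-cancer deaths, and does not turn the main curve into RFS or into a recurrence risk.

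Finally, it is tempting to say that cancer deaths with undocumented relapse are censored. The article censors those who die without recurrence. It provides for record linkage, chart review, phone contact and adjudication, and the classification of such deaths may sit in the full protocol.

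**Conclusion.** The point holds as a mismatch between the name of the primary endpoint, its definition and its descriptive estimator. It follows from the text and needs no assumption. The comparison itself is a valid test of the recurrence hypothesis, and the sample size fits that test.

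The Kaplan-Meier figures labelled RFS would be too high as RFS, by 1.6 to 6.4 points in GAS for an assumed 2% to 8% risk of death without recurrence under constant, independent hazards. As recurrence risks they would be slightly too high, by about half a point at 5%. A conclusion that RFS is higher would go beyond what was tested. The locoregional and metastasis endpoints share the defect.

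**What to change.** Make name and definition agree, before group allocation is opened.

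**Route that keeps the sample size.** Rename the primary endpoint time to recurrence, and rename the locoregional and metastasis endpoints likewise. Keep the log-rank test and the cause-specific Cox model. Replace the Kaplan-Meier curves by cumulative incidence with all deaths competing, unconditionally. Report true RFS (recurrence, metastasis or death from any cause, whichever comes first) as a key secondary outcome beside overall survival. Align the Abstract hypothesis, the sample-size text and the title of Table 2. The cost is wording in the protocol, registry entry and analysis plan; Table 1 already collects the dates of recurrence, metastasis and death and the cause of death.

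**Route that keeps RFS as primary.** Count death from any cause as an event, and restate the event rate and power. This changes the hypothesis. At an assumed 5% death risk the planned size gives between about 69% and 86% power, depending on whether anaesthesia affects those deaths, so the sponsor would have to justify an assumption on that and may need more patients.

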However, anesthetic medication types may have disparate effects on cancer recurrence (Melamed et al. 2003). Preclinical and biomarker studies have shown that volatile anesthetics might promote immunosuppression and create a pro-malignant environment including upregulation of hypoxia-inducible factor that supports cancer cell proliferation, migration, and angiogenesis, whereas propofol may preserve cell-mediated immunity and inhibit tumor angiogenesis (Buckley et al. 2014; Cho et al. 2017; Hiller et al. 2018a; Hiller et al. 2018a; Iwasaki et al. 2016; Jaura et al. 2014; Kim and Reviews 2017; Looney et al. 2010; Markovic-Bozic et al. 2016; Melamed et al. 2003; Tavare et al. 2012; Wall et al. 2019).

Despite the availability of biologically plausible explanations, clinical evidence that propofol-based total intravenous anesthesia (TIVA) can reduce tumor recurrence after curative resection remains inconsistent (Chang et al. 2021; Enlund et al. 2022; Hasselager et al. 2021; Hovaguimian et al. 2021; Jun et al. 2017; Lai et al. 2019; Lee et al. 2016; Makito et al. 2020; Wigmore and Farquhar-Smith 2016; Yoo et al. 2019; Yoon et al. 2022; Zheng et al. 2018), mainly because previously conducted studies have been retrospective or observational in nature. Given the risk of residual confounding inherent in observational studies, randomized trials are required to evaluate the influence of anesthetics on oncologic outcomes.

In this multinational, multicenter clinical trial, we will test the hypothesis that local or metastatic recurrence after curative resection of NSCLC is lower in patients randomized to propofol-based total intravenous anesthesia (TIVA group) than in patients randomized to volatile anesthesia (GAS group). Secondary hypotheses are that overall survival (OS) is increased when patients receive TIVA rather than GAS anesthesia and that postoperative complication rates are not different between the TIVA and GAS anesthesia groups.

In this report, we outline our approach and study protocol to establish an a priori record of the proposed study methods and endpoints.

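### The primary outcome is named recurrence-free survival, but deaths without prior recurrence are censored, so the endpoint is time to recurrence and the Kaplan-Meier RFS rates are mislabelled

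*Protocol article*

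**What the plan says.** Primary and secondary outcomes: "The primary outcome of this study is recurrence-free survival (RFS) after curative resection of NSCLC". The time variable then runs from surgery to the "earliest date between the recurrence/metastasis date and the last follow-up date due to death from any cause", with other reasons for ending follow-up listed after it. Death therefore sits in the censoring clause. Measurements repeats the rule: "Patients who die without local recurrence or metastatic disease will also be censored at the time of death".

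The locoregional and metastasis endpoints inherit it: "The observed time-to-events for LRFS and MFS are defined similarly to that of RFS". In the same paragraph, overall survival counts death from any cause as its event and cancer-specific survival counts cancer death. No passage counts death as an RFS event.

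The Background hypothesis concerns recurrence: "local or metastatic recurrence after curative resection of NSCLC is lower in patients randomized to propofol-based total intravenous anesthesia". The Abstract states the hypothesis in terms of RFS.

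Under the heading Analyses of primary outcome, the plan is: "The rates of RFS will be estimated using the Kaplan–Meier method and will be compared between two intervention groups using two-sample log-rank tests". As a sensitivity analysis, "Fine and Gray’s test will be used to compare cumulative incidence curves for RFS if competing risks due to non-cancer deaths exist".

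Sample-size calculations use a 3-year recurrence rate of 20% in the GAS arm. The Table 2 caption calls the assumed rates RFS rates, while its footnote defines the risk reduction as a difference in recurrence rates.

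**The concern.** The name promises one quantity and the definition delivers another. Recurrence-free survival counts recurrence or death from any cause. An endpoint that censors death without recurrence is time to recurrence, analysed through the cause-specific hazard. Either is a legitimate choice, but the plan uses the name of one and the rule of the other, for the primary outcome and for LRFS and MFS.

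This goes beyond wording because absolute rates are to be reported. A Kaplan-Meier curve that censors deaths estimates the chance of staying recurrence-free in a setting where nobody dies first. A reader shown a 3-year RFS of 80% will take it as the share alive without recurrence, which is lower as soon as anyone dies without recurrence. A difference between anaesthetics in death without recurrence would also leave a result labelled as survival untouched.

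**Working it through.** **Inputs from the protocol.** GAS 3-year recurrence 20%, hazard ratio (HR) 0.83 (1/HR 1.2), two-sided alpha 0.05, power 80%, 1:1 allocation, 4845 evaluable, 10% dropout, 5384 enrolled (Sample-size calculations, Table 2, Randomization).

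**Input assumed.** d, the net 3-year risk of death without recurrence. The documents give none; 2%, 5% and 10% are shown. Hazards are taken as constant and the two causes as independent.

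**Step 1: reproduce the plan's N.** Events = (1.960 + 0.842)² / (0.25 × lnHR²) = 7.849 / (0.25 × lnHR²). With |lnHR| rounded to 0.18 (HR about 0.835) this is 7.849 / 0.0081 = 969. Then 969 / 0.20 = 4845, and 4845 / 0.90 = 5383.3, so 5384. Both figures reproduce exactly. (Unrounded 1/1.2 gives 945 events and N = 4725; HR exactly 0.83 gives 905 and 4525.) The 20% used here is recurrence only.

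**Step 2: level in the GAS arm.** H_rec = −ln(0.80) = 0.2231; H_death = −ln(1 − d).
- Kaplan-Meier with deaths censored = exp(−H_rec) = 80.0% for every d.
- Truly alive and recurrence-free = exp(−H_rec − H_death) = 0.80 × (1 − d).
- Cumulative incidence of recurrence = H_rec / (H_rec + H_death) × (1 − the line above).

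| d | Kaplan-Meier RFS | Alive and recurrence-free | Overstatement | 1 − Kaplan-Meier | Cumulative incidence |
|---|---|---|---|---|---|
| 2% | 80.0% | 78.4% | 1.6 points | 20.0% | 19.8% |
| 5% | 80.0% | 76.0% | 4.0 points | 20.0% | 19.5% |
| 10% | 80.0% | 72.0% | 8.0 points | 20.0% | 19.0% |

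A simulation of 400,000 patients per scenario agrees: Kaplan-Meier about 80.0% each time, against 78.4%, 76.0% and 72.0% alive and recurrence-free.

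**Step 3: between-arm difference, same d in both arms.** TIVA Kaplan-Meier = 0.80^0.83 = 83.09%, so the Kaplan-Meier difference is 3.09 points. The true difference in the share alive and recurrence-free is 3.09 × (1 − d): 3.03, 2.94 and 2.78 points at d = 2%, 5% and 10%. The difference in cumulative incidence of recurrence is 3.06, 3.02 and 2.95 points.

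**Step 4: d differs by arm (illustration only).** With d = 5% in GAS and 8% in TIVA, the true shares are 0.80 × 0.95 = 76.0% and 0.8309 × 0.92 = 76.4%, a difference of 0.4 points. The planned analysis would still show 80.0% against 83.1%.

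**Step 5: if death were counted as an event.** With no anaesthetic effect on those deaths, the composite HR is (0.83 × H_rec + H_death) / (H_rec + H_death) = 0.844, 0.862 and 0.885 at d = 2%, 5% and 10%. Power at 4845 would be about 75%, 69% and 60%, and the evaluable N for 80% power about 5450, 6300 and 7840.

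**The case against.** The strongest defence is that the document discloses what it measures. It calls the variable a time to recurrence right after naming RFS, states the censoring rule openly, hypothesises about recurrence, estimates a hazard ratio for recurrence, and sizes the trial on a recurrence rate. All of this stands. It shows that the name and the reported rates are out of line with everything else, and it means that the log-rank and Cox comparisons are valid cause-specific analyses.

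A reader might infer that an error of 1.6 to 8.0 points swamps the 3-point target. The documents do not support that. The error is in the level of one arm, while the target is a difference between arms, defined in the Table 2 footnote as a difference in recurrence rates. With equal death risk that difference barely moves (step 3). A reader might also infer that all deaths are censored. Only deaths without prior recurrence are; a patient who dies after recurrence already counts as an event.

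It can further be said that competing risks are covered, since any non-cancer death would trigger the sensitivity analysis, and that overall and cancer-specific survival would reveal a mortality difference. This is partly right: such a difference would not be hidden from the trial as a whole. But the sensitivity analysis names non-cancer deaths only, addresses the incidence of recurrence rather than survival without it, and leaves the primary Kaplan-Meier rates as they are. The other survival outcomes do not correct the primary label.

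**Conclusion.** The point holds as a mismatch between name and definition that carries through to the reported absolute rates. The direction is certain: if anyone dies without recurrence, the Kaplan-Meier figure lies above the share alive and recurrence-free. The size is not certain. The 1.6 to 8.0 points per arm, and the 0.2 to 1.0 points by which one minus Kaplan-Meier overstates recurrence incidence, rest on an assumed 2% to 10% net risk of death without recurrence and on constant, independent hazards.

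The treatment contrast is little affected if such deaths are balanced: about 0.3 points at most, from 3.09 to between 2.78 and 3.03. If they are not balanced, the result labelled RFS would not show it. Nothing in the documents suggests an imbalance, so step 4 illustrates the blind spot and predicts nothing. The primary test is not invalid, and the sample size is not wrong for a recurrence endpoint.

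**What to change.** Reconcile name and definition; the sponsor should say which was meant.

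**Route (a), consistent with the hypothesis and the sample-size basis.** Rename the endpoint time to recurrence throughout, and likewise time to locoregional recurrence and time to metastasis. Keep log-rank and Cox as cause-specific analyses. In place of the Kaplan-Meier rates, report 3-year cumulative incidence by arm with death as a competing event (Aalen-Johansen), with the between-arm difference and 95% CI, unconditionally. Add true RFS (recurrence or death from any cause) as a supportive analysis. Cost: wording and one added analysis. Table 1 already collects dates of local recurrence, metastasis and death, and N is unchanged.

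**Route (b), if true RFS was intended.** Count death from any cause as an event in the primary definition, delete the censoring sentence in Measurements, and apply the same decision to LRFS and MFS. Then re-derive the event rate, hazard ratio and stated power, because 4845 rests on recurrence only. Cost: a new sample-size justification and possibly a larger trial, as step 5 indicates under its assumptions.
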